**Stationary environment**			
		⇨ Dorsal extension against different resistances	⇨ grasping, lifting, turning different cups (size, weight)
		⇨ Palmar flexion against different resistances	⇨ catching different balls on a marple run (reaction)
		⇨ Ulnar-/radial abduction against different resistances	⇨ compressing softballs of different sizes/hardness
	**Intertrial variability**	⇨ Supination/pronation against different resistances	⇨ pulling a cloth across the table (ulnar/radial) against different resistances
		⇨ Swimming in turbulent water	⇨ bowling/rolling a ball towards a partner
			⇨ playing ping-pong
			⇨ juggling with one hand

The training protocol for MT and MP after distal radius fracture follows the standardized method of the Mental Gait Training[43, 52]. It consists of several sequential steps: (1) description and (2) instruction of wrist movements; (3) the physical training with the unaffected side in alteration with either MP (with both wrists) or MT (only with the unaffected side); (4) building and strengthening of the motor representation of wrist movements, and (5) the physical execution of wrist movements (providing that the actual sensation does not disturb the mental image) (see Figure 2).

**Figure 2 Fig2:**
[figure not shown]
**MT and MP procedure after distal radius fracture (modified from**[43, 52, 53]**).**

In a first step the therapist discusses with the patient wrist movements the patient executes on a typical day. Both develop a therapy plan together in order to define which movements should be addressed during therapy. In the next step the patient is confronted with the physiological model of wrist movements, the movement descriptions. A movement description is the objective, biomechanical representation of the wrist movement using here the unaffected hand of the patient as a model. This method is used to provide the relevant functional aspects of the reference movement. Additionally, in order to achieve greater learning and retention results, the patients are prompted to verbalize the movements from an individual inside view addressing as many sensory modalities from memory as possible. The next step consists of the elaboration of the key characteristics of the different wrist movements. Finally, the key characteristics are marked symbolically, i.e. they are renamed as individual short formulae (e.g. up – centered or pull - release for dorsal flexion). The aim is the compression of the information (chunking). The image should be approximated thus to the dynamism and the temporal duration of the real movement[54].

After finalizing the movement descriptions the patients in the MP group execute movements with their unaffected side to provide additional feedback such as posture, muscle tension, or joint positions. The physical training distinguishes itself by a sort of proprioceptive training in which under modification of perception, movement and environment the movement representation should be further stabilized and differentiated. The key characteristics for flexion were *up-centered*, and for the ulnar and radial deviation *inwards-centered-outwards-centered*. Following the physical training with open and closed eyes to enhance kinesthetic perception, the patients in the MP group imagined normal wrist movement with the unaffected side with different imagery modalities (kinesthetic, visual; for examples see Table 2) with the following sequence (modified from[43]):

**Table 2 Tab2:** **Examples of mental practice script delivered to MP group**

Visual:	How does your hand look turning a door key? Imagine seeing your hand, the key, and the door. See your wrist turning and the forearm pronating.
**Kinesthetic:**	Imagine touching the cold metal of the key with your fingers. Now feel your muscles in your forearm and hand activate as you grasp and turn the key. What can you feel? Is there a tension in your muscles?

Active execution with the unaffected side (1 x with open eyes)Visual imagery (1 x unaffected side, 1 x affected side; with closed eyes)Active execution with the unaffected side (1 x with closed eyes)Kinesthetic imagery (1 x unaffected side, 1 x affected side; with closed eyes).

After establishing the internal concept of wrist movements, the systematic training phase with physical training alternating with MP follows this protocol:Active execution with the unaffected side (2 x with open eyes)Active execution with the unaffected side (2 x with closed eyes)Kinesthetic imagery with the unaffected side (1 x with closed eyes)Kinesthetic imagery with the affected side (5–10 x with closed eyes)

Due to the findings of Yae et al.[55], that mental imagery is most effective with a kinesthetic focus, our training process is aiming at that modality.

Patients in the MT group immediately start with the observation of the movements with the unaffected side in the mirror. During MT the affected hand remains hidden from view behind the mirror, which is placed in the midsagittal plane of the participant. The patient is observing the reflected image of the unaffected hand, which appears like the affected side performing the movement. Patients perform each wrist movement with the unaffected side 8 to 10 times with visual focus on the mirrored picture of the healthy side.

The overall aim of these protocols is to preserve motor representation of hand function to enable patients to execute wrist movements with high accuracy and appropriate strength after splint removal.

The control group receives relaxation training to achieve the same total amount of time the therapist spends with the patients of the experimental groups.

### Outcome measures

The assessments focus on changes in three key domains: subjective wrist function (PRWE-G; DASH), objective impairment (Range of motion, grip strength) and quality of life/social engagement (DASH, EuroQol).

#### Primary outcome

Is the subjective rating of pain and impairment in activities of daily life (*Patient-rated Wrist Evaluation; PRWE-G*, German version,[56]), a validated tool for assessing functional outcome in patients with distal radius fracture[57]. The questionnaire is completed by the investigator via patient interview and consists of two domains, pain and function. There are five items in the pain domain (e.g. “Rate your pain when lifting a heavy object.”) and ten items in the function domain (e.g. “Rate your difficulty you experience when fastening buttons on your shirt.”). The response to each item is scored on a scale of 0 to 10. Scores of each individual item were provided with qualitative descriptors defined as: none (0), minimal (1–2), mild (3–4), moderate (5–6), severe (7–8) or very severe (9–10). The pain score is the sum of five items, with the worst possible score of 50, and the disability (function) score is the sum of ten items divided by 2.

#### Secondary outcomes

The *Disabilities of the Arm, Shoulder and Hand (DASH*;[58]) score is a 11-item, self-administered questionnaire designed to measure physical functions, symptoms, and social function, work, sleep, and confidence items in patients with any or several musculoskeletal disorders of the upper limb. The DASH outcome measure is scored in two components: the Disability/Symptom and the optional high performance Sport/Music module. The DASH Disability/Symptom score is a summation of the responses to 11 questions on a scale of 1 (without difficulty or no symptom) to 5 (unable to engage in activity or very severe symptom). This value is then transformed to a score out of 100 by subtracting one and multiplying by 25 with values between 0 (no disability) and 100 (severe disability). The questions examine the degree of difficulty in performing a variety of physical activities because of arm, shoulder, or hand problems (6 items). It also investigates the severity of pain, tingling (2 items), as well as the effect of the upper limb problem on social activities, work, and sleep (3 items).

*Range of motion (ROM)* of the radiocarpal joint is measured on both sides with a handheld goniometer. Four parameters are evaluated: dorsal extension, palmar flexion, radial and ulnar abduction of the wrist joint[59].

*Grip strength* is measured with a handheld dynamometer (Myon, Prophysics), and carried out three trials on each side. If necessary, the instrument is adjusted to the size of the patients’ hands. The patient is sitting in a chair, her upper arm by her side of the body and the forearm stretched to an angle of 90°, with the elbow supported. The patient is encouraged to squeeze the dynamometer as hard as possible. A mean value is determined according to the standardized Mathiowetz procedure[60]. The grip strength is presented as the percentage of the value of the injured side of the value of the uninjured side. In order to account for hand dominance in grip strength, if the non-dominant hand was injured, the percentage will be multiplied by 1.10; if the dominant hand was injured, the percentage will be multiplied by 0.90[61].

Social engagement is evaluated with the social functioning subscale of the DASH-Questionnaire[58] and health related quality of life with the EQ-5D[62]. The EQ-5D is a short questionnaire with five dimensions (mobility, self-care, usual activities, pain or discomfort, and anxiety or depression), each of which can be rated at one of three levels (1 no problem, 2 some problems, 3 extreme/severe problems). EQ-5D utility scores range between a full health score of 1 (where the respondent has no problems on any dimension) and the lowest score of -0.59 (when the respondent reports that they are at the bottom level of each dimension).

Additionally, falls associated self-efficacy is evaluated (ABC-Scale, German version,[63]). Demographic information is analyzed at the beginning of the intervention period.

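### The DASH scoring rule leaves out the division by the number of items, so as written it gives 250 to 1350 rather than the stated 0 to 100

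*Protocol article*

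**What the plan says.** The rule is in the first paragraph of Secondary outcomes in the protocol article. It has four parts:

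- The raw score is a sum: "The DASH Disability/Symptom score is a summation of the responses to 11 questions".
- Each item is rated "on a scale of 1 (without difficulty or no symptom) to 5 (unable to engage in activity or very severe symptom".
- The transformation follows directly: "This value is then transformed to a score out of 100 by subtracting one and multiplying by 25".
- The result is said to lie on a 0–100 scale, "with values between 0 (no disability) and 100 (severe disability".

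The same paragraph divides the items into groups of 6, 2 and 3. Neither this paragraph nor any other part of the article mentions an average, or a division by the number of items, for the DASH. For the PRWE function score, under Primary outcome, the article does give the divisor: the ten items are summed and halved.

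Under Statistical analysis, the article says that missing data will be imputed. It does not say whether this covers single questionnaire items or only whole assessments.

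**The concern.** The value being transformed can only be the sum named in the sentence before it. Subtracting one and multiplying by 25 turns a number between 1 and 5 into a number between 0 and 100. That suits a single item or an item mean, but not a sum of 11 items. The rule and the range it claims therefore cannot both be right.

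What is at stake is how a prespecified secondary outcome is reported. The Outcome measures section uses the DASH in two of its three domains: subjective wrist function, and quality of life/social engagement. If the rule were programmed literally, DASH results would be on a scale the article does not describe, and a reader could not place them between its two anchors of no disability and severe disability.

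**Working it through.** **Inputs**, all from Secondary outcomes: 11 items; item range 1 to 5; transformation (value − 1) × 25; stated range 0 to 100. The item groups add up (6 + 2 + 3 = 11), so a wrong item count does not explain the mismatch.

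**Step 1: try to reproduce the stated range.** Let S be the item sum. Its minimum is 11 × 1 = 11 and its maximum is 11 × 5 = 55.

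- Lowest score as written: (11 − 1) × 25 = 250.
- All items rated 3: S = 33, so (33 − 1) × 25 = 800.
- Highest score as written: (55 − 1) × 25 = 1350.

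The stated 0 to 100 is not reproduced. The width is 1350 − 250 = 1100 instead of 100.

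**Step 2: see which reading gives 0 to 100.**

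| Reading | All items 1 | All items 5 |
|---|---|---|
| (S − 1) × 25, as written | 250 | 1350 |
| One subtracted from each item before summing: (S − 11) × 25 | 0 | 1100 |
| (S − 1)/11 × 25 | 22.7 | 122.7 |
| S/11 × 25 − 1 | 24 | 124 |
| Item mean: (S/11 − 1) × 25 | 0 | 100 |

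Of these, only the item mean gives the stated range. It puts the middle form (S = 33) at (3 − 1) × 25 = 50.

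**Step 3: relate the two scores on complete forms.** Let D = (S/11 − 1) × 25 be the 0–100 score. Then 11 × D + 250 = 25S − 275 + 250 = 25S − 25 = (S − 1) × 25, which is the written score. Checks: D = 0 gives 250, D = 50 gives 800 and D = 100 gives 1350.

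The constant 250 cancels in any difference between arms or between visits, while the factor 11 remains. A true difference of 10 points would be reported as 110. Means carry both the factor and the constant. Because the relation is linear and the same for every patient, F statistics, p-values and standardised effects are identical.

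**Step 4: unanswered items, conditionally.** Assume a blank adds zero to the sum and is not imputed. An item that would have been rated 3 then lowers the written score by 3 × 25 = 75. On the 0–100 scale this is 75/11 ≈ 6.8 points, in the direction of less disability.

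**The case against.** The strongest reply is that nobody would be misled. The sentence states the target range, and the item mean can be recovered from it. A literal calculation gives at least 250 on a scale that ends at 100, so the slip would show on the first complete form. The likeliest explanation is a lost averaging step in the description of a cited instrument, and the scoring program may well be right. This is a fair argument about weight, and it is why the point is minor. It does not make the sentence correct: the article chose to state the formula, and the formula contradicts the range beside it.

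Several stronger readings are tempting, but the article does not support them.

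- A reader might infer that the DASH comparisons would be invalid. On complete forms they would not be, because the error is a linear rescaling.
- A reader might take the DASH as the main secondary outcome because it comes first. The article states no hierarchy among secondary outcomes.
- A reader might conclude that skipped items will bias the scores. That requires blanks to count as zero, which the article does not say, and the imputation sentence may cover them.
- A reader might extend the error to social engagement, since "Social engagement is evaluated with the social functioning subscale of the DASH-Questionnaire". The article gives no formula for that subscale, so there is no arithmetic there to be wrong. Its scoring, like a minimum number of answered items, is detail that an article may leave to the full protocol.

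**Conclusion.** The DASH scoring rule is wrong as written. Applied literally to complete forms it gives scores from 250 to 1350, because the division by the number of items is missing. Arm differences and confidence intervals would be 11 times those on the 0–100 scale, and means would be shifted by a further 250. Hypothesis tests on complete forms would be unchanged. The effect of about 6.8 points for one skipped item depends on blanks adding zero to the sum without item-level imputation, which the article leaves open.

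The conclusion rests on two readings of the text: that the transformed value is the sum just defined, and that 0 to 100 is the intended range. Nothing in the article shows that any data have been scored this way. The primary outcome is the PRWE, and the sample size is based on it, so neither is affected. This is a minor correction to a secondary outcome.

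**What to change.** Replace the transformation sentence with: score = (sum of responses / number of items answered − 1) × 25, range 0 to 100. Then check that the scoring program uses this form by running three test forms with all items at 1, 3 and 5; they should return 0, 50 and 100.

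The cost is one clause of text and a short program check. The design, the sample size and the analysis model stay as they are.

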### Procedure

All patients give written informed consent prior to the study. Before randomization, the patients complete the Controllability of Motor Imagery Test[47] to control for the ability to perform and control a mental image of a movement, which is essential for successful imagery training. After baseline assessment, randomization is performed by an independent department (Department of Biometrics at Ulm University).Assessment of primary and secondary outcomes takes place upon entry to the study (T1) by a blinded assessor and is repeated after 3 weeks (T2), 6 weeks (T3), and 12 weeks (T4, follow-up) after the beginning of the training program (see Figure 1).

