**Table 1 Tab1:** **Movement tasks based on Gentile’s taxonomy of tasks**[51]

		Body stability	
		No object manipulation	Object manipulation
		⇨ dorsal extension	⇨ lifting up weight (dorsal extension)
		⇨ palmar flexion	⇨ lifting up weight (palmar flexion)
		⇨ ulnar-/radial abduction	⇨ wiping a table with a cloth
		⇨ supination/pronation	⇨ handling of a bike lock/kitchen timer
	**No intertrial variability**	⇨ opening and closing hand (like grasping a cup)	⇨ wringing out a towel
		⇨ thumb-finger-oppositions	⇨ compressing a softball
		⇨ finger-tapping sequence	⇨ grasping a pen with little finger (e.g.) and thumb
			⇨ playing piano (simple 5-finger-scale)

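### Grip strength is scored against the uninjured hand with the denominator not fixed at baseline, and allocation may change that hand's strength

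*Protocol article*

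**What the plan says.** **Scoring rule.** Under Secondary outcomes, the protocol article measures grip by dynamometer, "carried out three trials on each side", takes a mean, and then gives the rule: "The grip strength is presented as the percentage of the value of the injured side of the value of the uninjured side". A constant is applied for hand dominance: "if the non-dominant hand was injured, the percentage will be multiplied by 1.10", and by 0.90 if the dominant hand was injured. The visit that supplies the denominator is not named.

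**Visits.** Under Procedure, baseline assessment (T1) comes before randomisation, and assessment "is repeated after 3 weeks (T2), 6 weeks (T3), and 12 weeks (T4, follow-up").

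**Training of the uninjured hand.** The Intervention section, after Table 1, lists as the third training step for both experimental arms "the physical training with the unaffected side in alteration with either MP (with both wrists) or MT (only with the unaffected side"). For MT: "Patients perform each wrist movement with the unaffected side 8 to 10 times". For MP, each sequence of the systematic phase opens with "Active execution with the unaffected side (2 x with open eyes") and two more with eyes closed, followed by imagined repetitions. Table 1 includes tasks that load grip or resist movement, for example "compressing a softball", lifting a weight and wringing a towel. Object manipulation and intertrial variability are higher difficulty levels, tried once a patient rates a task 4 or lower.

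**Control.** The control arm receives relaxation training matched for therapist time. The Intervention section also says, however, that from week 4 every patient is given illustrated instructions for the movement tasks.

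**The concern.** A ratio to the opposite hand works as a recovery measure if that hand is a stable reference that treatment does not touch. Here two of the three arms are assigned to exercise it between T1 and the later visits. If the denominator is the same-visit value, it is a post-randomisation quantity that allocation can change.

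A stronger uninjured hand lowers the percentage even if the injured hand has recovered equally well. The dominance multipliers do not correct this. They are fixed for each patient and merely scale the distortion by 1.10 or 0.90.

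At stake is the interpretation of one of the two objective impairment outcomes (range of motion and grip), in a trial of 13 patients per arm. A null or adverse grip result could mean no benefit to the injured hand, or it could mean a stronger healthy hand. The ratio alone cannot tell these apart.

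**Working it through.** The document states no figure on this point that could be reproduced, so the check is ratio algebra with assumed inputs.

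**Inputs from the document**
- Outcome: 100 × injured / uninjured (Secondary outcomes).
- Scheduled sessions in weeks 1-3: 3 × 5 = 15. In weeks 4-6: 3 × (3 guided + 2 unguided) = 15. Total: 30 (Intervention).
- Active repetitions with the uninjured hand: MT 8 to 10 per movement; MP 2 + 2 = 4 per sequence of the systematic phase.

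**Inputs assumed, because the document gives none**
- R, the ratio without any training effect: 40%, 60% or 80%.
- g, the relative gain in uninjured-hand grip over control: 2% to 15%.
- c, the share of that gain carried over to the injured hand: 0 or 0.5, with 1 as the limiting case.

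**Formula.** The reading in a trained arm is R × (1 + c·g)/(1 + g), and in control it is R. The shift is R × [(1 + c·g)/(1 + g) − 1], which is negative for any g > 0 with c < 1.

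**Results at R = 60%**

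| g | Reading, c = 0 | Shift (points) | Reading, c = 0.5 | Shift (points) |
|---|---|---|---|---|
| 2% | 60/1.02 = 58.8 | −1.2 | 60 × 1.01/1.02 = 59.4 | −0.6 |
| 5% | 60/1.05 = 57.1 | −2.9 | 60 × 1.025/1.05 = 58.6 | −1.4 |
| 10% | 60/1.10 = 54.5 | −5.5 | 60 × 1.05/1.10 = 57.3 | −2.7 |
| 15% | 60/1.15 = 52.2 | −7.8 | 60 × 1.075/1.15 = 56.1 | −3.9 |

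With c = 0, the shift over the same range of g is 0.8 to 5.2 points at R = 40% and 1.6 to 10.4 points at R = 80%. With c = 1 the reading stays at R: there is no spurious loss, but the injured hand's own gain does not show either.

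**MP against MT.** If, as an assumption, g were 5% in MP and 10% in MT, with c = 0 and R = 60%, the readings would be 57.1% and 54.5%. That is a gap of about 2.6 points in favour of MP with no difference in the injured hand.

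**Effect of fixing the denominator.** Assume 20 kg for the uninjured hand at T1 and, at a later visit, an injured hand of 12 kg in control and 13.2 kg in a trained arm (a true benefit of 10%).
- T1 denominator: 13.2/20 = 66.0% against 12/20 = 60.0%, a difference of +6.0 points for every g.
- Same-visit denominator, 13.2/(20 × (1 + g)): 64.7%, 62.9%, 60.0% and 57.4% for g = 2%, 5%, 10% and 15%, against 60.0% in control.

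The disappearance of the benefit at g = 10% only reflects that both hands were assumed to gain 10%. It shows the mechanism and is not a forecast.

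**The case against.** The strongest reply is that nothing in the document shows uninjured-hand grip to rise more in MP or MT than in control.

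- **The load may be light.** Most MP content is imagined. Loaded tasks come only at higher difficulty levels, movements are chosen in an individual plan, and no strengthening dose is stated. The stated aim is to preserve motor representation.
- **Control may not be untrained.** All patients receive usual therapy, and the week-4 instructions are said to go to everyone.
- **Carry-over would shrink the shift.** If training one hand also strengthens the other, the ratio moves less.
- **The denominator's visit is inferred.** The article is condensed, and describing how grip is presented does not rule out an analysis of raw values.
- **The same-visit ratio has a merit.** It adjusts for effort and general condition on the day.

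Most of this stands, and it limits the point. A reader might infer that the grip outcome is biased as a matter of fact, that control patients do nothing but relax, or that MP and MT are equally exposed. The document supports none of these: the gains are unknown, the week-4 wording cuts against the second, and the active repetitions differ about twofold (4 against 8 to 10).

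The reply does not remove the structural problem. The article states its scoring rule in detail, down to the dominance multipliers, without anchoring the denominator at T1, and both experimental arms are assigned physical work with the hand that supplies it.

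**Conclusion.** The point holds in conditional form. As written, the denominator may respond to allocation. The ratio is biased against MP and MT to the extent that training raises uninjured-hand grip proportionally more than it carries over to the injured hand. Because MT exercises that hand more than MP, the comparison between them can be distorted too.

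The size cannot be determined from the document. The range of 0.6 to 7.8 points rests on three assumptions: an untrained ratio of 60%, a gain of 2% to 15% over control, and carry-over of half or none. It also takes the same-visit reading of the denominator. If control patients train the uninjured hand as well, g is smaller and so is the shift.

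A reader might extend the point to the trial's main conclusion or to range of motion. Neither follows. The primary outcome, PRWE, does not use this ratio. Range of motion is measured on both sides but is not expressed as a percentage of the other side.

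**What to change.** Analyse injured-side grip in absolute units, adjusted for T1 grip of both sides and for whether the dominant hand was injured. If injured-side grip could not be taken at T1 in some patients, the T1 uninjured-side value and dominance still serve as covariates. If a percentage is wanted, divide by the T1 uninjured-side value at every visit and say so. In either case, report uninjured-side grip by arm and visit, so that any training effect on that hand can be seen. It would also help to state whether the week-4 movement-task instructions go to the control arm.

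The change is to the stated analysis rule and needs no new data: both sides are already measured, and T1 precedes randomisation. The cost is losing the same-visit ratio's adjustment for day-to-day effort. That ratio can be kept as a supportive presentation beside the main analysis.
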